### Data monitoring

Weekly reports are generated to track the frequency of tool triggering, calculator completion, and smart set usage by clinic. This will allow us to determine if iCPR is being used and review trigger rates at each clinic to evaluate issues with triggering. If provider use of iCPR is lower than expected, we will contact clinic medical directors and managers to determine potential issues with the tool. We will also perform intermittent chart review to ensure that iCPR is triggering properly and data collection is correct. Modifications to iCPR to improve usage or data collection may be made based on the findings of the data monitoring. A data monitoring committee is not required since there is minimal risk of harm from using the CDS that supports guideline-based care.

### Statistical analysis

Planned statistical analyses include comparison of patient and provider characteristics between groups to evaluate for group balance. Descriptive statistics will be used to show the use of iCPR components in the intervention group. A three-level logistic regression model with a random effect for practice and one for provider within practice will be used to assess the primary outcome and other clinical outcomes. A fixed effect will be included for intervention and for randomization strata. Subgroup analysis by primary institution (Wisconsin or Utah) and provider training will be performed. An interim analysis will be done 1 year after the last clinic receives academic detailing. Comparison of iCPR component use based on provider training and gender will be performed using a three-level logistic regression model with a random effect for practice and for provider within practice with fixed effects for provider training and gender.

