### Randomization

A computer-generated, blocked, stratified-randomization scheme was performed at the level of the clinic. Stratification was by institution and by the number of patient visits to the clinic in the previous year that would have triggered the iCPR tool. Three strata of visits were used: <750, 750–1500, and >1500. Group assignment was performed by the study statistician.

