### Tool design considerations

The team also reviewed all of the iCPR tool features and designs to ensure it met the needs of the diverse clinics. This included examining the (1) tool activation level, (2) timing of alerts, (3) integration into clinical workflow, (4) alert triggers, and (5) interruptive versus non-interruptive alerts.Tool activation: We chose to activate the tool based on the clinic where the encounter was performed instead of at the provider level. The clinic was chosen to coincide with the unit of randomization and to prevent study contamination from providers that worked at multiple clinics.Timing of alerts: It was clear from interviews with providers that there was variation in when they ordered tests and antibiotics during the patient encounter. We chose to base the main trigger on the reason for visit despite infrequent completion of this field by providers in the original iCPR clinical site [9]. Relying on reason for visit as the main trigger made iCPR available early in the encounter and throughout the subsequent workflow. We also included a secondary trigger, similar to the original iCPR design, that would occur toward the end of the encounter based on diagnosis and a combination of diagnosis and orders. While the secondary trigger may not be frequently used, it might allow providers to change decisions or at least alert them to considerations for future encounters. We also automatically triggered alerts in the provider’s inbox and when the provider reopened an encounter after a relevent test had resulted.Integration into clinical workflow: The iCPR needed to be integrated into active clinical practice without disrupting patient care. It is clear that without integration into workflow, CDS tools are not used [15]. This led to some individualization between institutions including the use of NoteWriter at some sites. We also decided to make iCPR as flexible as possible in order to facilitate the integration into various workflows. This included the ability for providers and nurses to use bundled ordersets based on test results and for support of telephone encounters or patient portal encounters.Alert triggers: Another guiding principle was limiting the number of inappropriate triggers. We balanced trigger sensitivity and specificity, erring on the side of specificity at the cost of missing some potentially appropriate encounters. Triggers were determined by reviewing clinic data from the previous year for the final encounter diagnoses based on available reasons for visit and whether antibiotics were prescribed. We found that only three reasons for visit commonly resulted in diagnoses that we wanted to affect. Based on these, we chose “cough/chest congestion,” “URI (upper respiratory infection),” and “sore throat” as the reason for visit triggers. For triggers based on diagnosis and antibiotics, we chose the narrowest diagnoses and only antibiotics commonly used in respiratory infections (Table 2).Interruptive vs non-interruptive alerts: Interruptive alerts interfere with workflow and force users to acknowledge the alert, potentially increasing clinician frustration and alert fatigue [16, 17]. Given the broad nature of the three reasons for visit triggers we chose, we knew that iCPR was likely to trigger at times when it would not be helpful, such as when a patient with asthma or sinusitis presented with a cough. Based on the risk of inappropriate triggers as well as provider opinions from the interviews, we chose to use non-interruptive alerts for the reason for visit triggers. We explored options for non-interruptive alerts for the diagnosis triggers, but there were no mechanisms within the EHR that allowed us to do this. Thus, we opted for interruptive alerts if iCPR was triggered by a diagnosis or diagnosis plus antibiotic prescription.

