### Power calculation

Sample size calculations were adjusted for clustering of patients within clinics. Prior year visit data from the University of Wisconsin and the University of Utah was used to estimate the number of iCPR triggers during the study period. We assumed 25 clusters or clinics with a control group antibiotic prescribing rate of 30–40% for iCPR eligible encounters and an absolute decrease of 10% in the rate of antibiotic prescribing in the intervention group. The intra-cluster coefficient was estimated to be between 0.01 and 0.05. Sample size calculations were performed with a significance level of 0.05 and 80% power. The estimated sample size for the most conservative assumptions (control group antibiotic prescription rate of 40% and intra-cluster coefficient of 0.05) is 52,457 patient encounters which, based on historical data, should be attained within 2 years.

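### The primary model leaves out each clinic's prior-year antibiotic prescribing rate: a valid analysis, but it gives up precision that matters near the upper end of the planned ICC range

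*Protocol article*

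**What the plan says.** All references are to the protocol article.

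- **Statistical analysis** gives the model form: "A three-level logistic regression model with a random effect for practice and one for provider within practice will be used to assess the primary outcome". It then names the fixed effects: "A fixed effect will be included for intervention and for randomization strata". No baseline prescribing measure is listed. The same section plans an interim analysis one year after the last clinic's academic detailing.
- **Randomization** defines the strata: "Stratification was by institution and by the number of patient visits to the clinic in the previous year that would have triggered the iCPR tool", with three volume bands.
- **Tool design considerations** shows that the triggers were chosen by "reviewing clinic data from the previous year for the final encounter diagnoses based on available reasons for visit and whether antibiotics were prescribed".
- **Power calculation** also draws on historical records: "Prior year visit data from the University of Wisconsin and the University of Utah was used to estimate the number of iCPR triggers". It takes an ICC of 0.01 to 0.05 and a 10-point absolute reduction, and states: "We assumed 25 clusters or clinics with a control group antibiotic prescribing rate of 30–40% for iCPR eligible encounters".
- **Table 1** gives the clinics enrolled: 22 + 11 = 33, of which 12 + 6 = 18 are intervention, leaving 15 controls.

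**The concern.** In a trial with few clusters and very many encounters per cluster, the standard error of the treatment effect comes almost entirely from differences between clinics. More encounters barely change it. Once the clinics are randomized, the remaining lever is to explain part of the between-clinic variance in the analysis. A clinic's own past prescribing rate is the natural candidate, because it measures the outcome before the intervention. Visit volume and institution are at best indirect substitutes.

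Two things are at stake. The first is power and interval width if the ICC lies near the top of the planned range. The second is chance imbalance in prescribing habit between 18 and 15 clinics, which the randomization strata do not directly control.

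**Working it through.** **1. The plan's own figure.** For 40% v 30%, two-sided alpha 0.05 and 80% power, individual randomization needs 356 per arm. With k clinics per arm, the encounters per clinic are m = n(1 − ICC)/(k − n × ICC), which requires k > n × ICC = 356 × 0.05 = 17.8. Twenty-five clinics give 12.5 per arm, so no finite number of encounters reaches 80%, and 52,457 is not reproduced. With unlimited encounters, power (normal test) tops out at about 65% with 25 clinics and about 77% with 33 (18 v 15). That is a separate matter in the power section. It matters here because it shows that at ICC 0.05 the number of clinics, not of encounters, sets the limit.

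**2. Where the variance lies.** Mean encounters per clinic: 52,457/33 = 1,590. At ICC 0.05 the between-clinic part is 0.05 and the within-clinic part 0.95/1,590 = 0.0006, so 0.05/0.0506 = 99% lies between clinics.

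**3. Chance imbalance.** At a 40% rate and ICC 0.05 the between-clinic SD is √(0.05 × 0.24) = 0.110. The SD of a chance difference in baseline rate between 15 and 18 clinics is √(0.012 × (1/15 + 1/18)) = 0.038. That is 3.8 points against a 10-point target effect.

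**4. Gain from the covariate.** Let r be the correlation between baseline and trial-period clinic rates left after the strata. Then

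Var = (0.24/15 + 0.21/18) × [ICC(1 − r²) + (1 − ICC)/1,590], where 0.24/15 + 0.21/18 = 0.02767.

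Power uses the noncentral t. Degrees of freedom are 33 − 1 (intercept) − 1 (intervention) − 5 (six strata taken as fully crossed) = 26, or 25 with the covariate. The half-width is t × SE. Cluster sizes are taken as equal, and the calculation is on the risk-difference scale as an approximation to the logistic model.

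Worked case, ICC 0.05:
- r = 0: SE = √(0.02767 × 0.0506) = 0.0374; half-width 2.056 × 0.0374 = 7.7 points.
- r = 0.5: SE = √(0.02767 × 0.0381) = 0.0325; half-width 2.060 × 0.0325 = 6.7 points.

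| ICC | r | Power | 95% CI half-width (points) |
|---|---|---|---|
| 0.05 | 0 | 73% | 7.7 |
| 0.05 | 0.3 | 77% | 7.4 |
| 0.05 | 0.5 | 84% | 6.7 |
| 0.05 | 0.7 | 95% | 5.5 |
| 0.03 | 0 | 91% | 6.0 |
| 0.03 | 0.5 | 97% | 5.2 |
| 0.02 | 0 | 98% | 4.9 |
| 0.02 | 0.5 | 99.6% | 4.3 |
| 0.01 | 0 | >99.9% | 3.5 |
| 0.01 | 0.5 | >99.9% | 3.1 |

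At ICC 0.05, r of about 0.40 is needed for 80% power on this t basis.

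**5. Cost if the covariate is useless.** With r = 0 at ICC 0.05, moving from 26 to 25 degrees of freedom changes power from 73.0% to 72.9%.

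**The case against.** The best defence is that nothing here is an error. The model matches the randomization and is valid as written. The article does not say that no other covariate may enter, and a fuller list could sit in an analysis plan that is not shown. This stands as to validity. The article does, however, name the primary model's fixed effects, so adding a baseline rate is a change that must be prespecified somewhere.

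The second defence is that the gain is confined to one end of the planning range. This also stands. On the same t basis, the planned model already has 82% power at ICC 0.04 for 40% v 30%, and 81% at ICC 0.05 for 30% v 20%. A reader might infer that the trial is short of power throughout and that the covariate is a large, free remedy. The documents do not support that. They give no value for r, institution and volume may already absorb some between-clinic variance, and there is a small cost in degrees of freedom and data extraction.

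A reader might also infer that every recorded encounter variable should be added, trigger type included. That would be unsafe. Table 2 contains triggers that exist only when an antibiotic was ordered, so trigger type depends partly on the primary outcome. Diagnoses are recorded after randomization, and the tool's own smart sets supply diagnoses.

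**Conclusion.** The point holds as lost precision, not as bias or invalidity. The primary model does not use a baseline measure of the outcome that the team was in a position to extract. At ICC 0.05 the gain is modest to substantial: 4 points of power at r = 0.3, 11 at r = 0.5 and 22 at r = 0.7. It is 6 points at ICC 0.03 with r = 0.5, under 2 points at ICC 0.02 with r = 0.5, and nil at ICC 0.01, where only the interval narrows. These figures rest on an assumed r, on 52,457 encounters spread equally over 33 clinics, on a two-sided 5% test, and on a linear approximation to the logistic model. Because the downside is so small, the change is worth making even with r unknown.

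**What to change.** Before outcomes are compared by arm, including at the 1-year interim, add one clinic-level fixed covariate to the primary model: the logit of each clinic's antibiotic prescribing rate in the 12 months before launch. Calculate it among encounters that meet the same eligibility definition as the trial analysis set, as far as prior-year records allow this to be reproduced, and state any departure.

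Patient age group may be added as an encounter-level covariate; date of birth is already collected. Do not adjust for trigger type beyond the recorded reason for visit itself.

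The cost is one prior-year EHR query covering all 33 clinics, one clinic-level degree of freedom and a sentence of analysis text.

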### Setting/clinic eligibility

The study is being conducted at primary care clinics associated with the University of Wisconsin and University of Utah medical centers. All General Internal Medicine (GIM) and Family Medicine (FM) primary care clinics at the two institutions were invited to participate. A total of 33 individual clinics (12 GIM clinics, 16 FM clinics, and 5 combined clinics) are participating in the study. Table 1 illustrates the clinic characteristics. Clinics were enrolled by site leads at each medical center. All physicians, nurse practitioners, physician assistants, and residents at participating clinics were eligible to participate. Both sites use the same EHR system (Epic Systems, Verona, WI) and had off-the-shelf capabilities to develop CDS tools in their EHR. Each site was supported by an information technology department that was able to develop and test the components of the iCPR before deployment.

**Table 1 Tab1:** Description of study clinics

	University of Wisconsin	University of Utah
Total no. of clinics	22	11
No. of intervention clinics	12	6
Total no. of providers	268	111
GIM clinics	10	2
FM clinics	12	4
Combined GIM and FM clinics	0	5
No. of providers per clinic	2–29	3–23

*GIM* General Internal Medicine, *FM* Family Medicine

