#### Comparing workflows

The current iCPR tool is adapted from the previous iCPR tool but tailored to fit the current sites’ unique workflows. The iCPR tool design was developed by an interdisciplinary team of experts in primary care, usability, and clinical informatics. Interviews were held with providers, clinic managers, and medical assistants at each site to determine general clinic workflows as well as specific workflows for rapid strep and chest x-ray testing.

These interviews demonstrated that workflows varied dramatically by institution with some variation by clinic and even by provider within a clinic. For example, a major difference between institutions was that University of Utah providers heavily leveraged an EHR-assisted documentation pathway called “NoteWriter.” This structured documentation template has the ability to create pick-list histories based on the patient’s chief complaint. In this workflow, medical assistants record a structured history that the provider then reviews and confirms with the patient. The structured history, as well as the vital signs and, if used, structured physical exam then populates the iCPR tool. This decreases the need for duplicate documentation. Another workflow difference was a variable approach among clinics to rapid strep testing including which clinic personnel review test results and whether patients remain in the clinic until results are complete.

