#### Alerts

At the University of Wisconsin, a standard EPIC alert is used to inform providers when a patient is appropriate for iCPR. Providers are familiar with seeing these alerts for other conditions. The alert specifies why iCPR was triggered and includes a link to the risk calculator. In addition to this alert, the University of Utah placed an additional tab in NoteWriter. This tab, called “Provider Score,” was populated with the appropriate iCPR criteria (Centor, McIsaac, and/or Heckerling) based on the reason for visit. In all other cases, it was blank. The Provider Score tab of NoteWriter draws information from vital signs and structured history and physical exam documentation. It can also be completed ad hoc. After completion, the score and interpretation are visible to the provider. The calculator score also drops directly into the clinical note.

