## Discussion

The multi-site iCPR trial builds on the previous single-site study to assess whether CPRs integrated in the EHR can change provider behavior and improve evidence-based care in a broad range of primary care clinics. We focused on the importance of integrating the tool into clinic workflows in order to optimize uptake and clinical usefulness. This required building flexibility into the tool to accommodate a variety of workflows and led to variations in the tool design and workflows between the two health systems. Near-live usability testing evaluated how well we succeeded in workflow integration and reaffirmed the importance of near-live usability testing when implementing new EHR tools. While we designed the tool to be provider-centric, we were forced to make some usability compromises based on limitations in the EHR. The limited points for iCPR triggering and lack of specificity of potential triggers were highlighted in usability testing. However, there were no clear solutions to these issues within the current EHR. EHR systems need to continue to evolve in order to better accommodate the diversity in workflow and clinical decision making. The impact of iCPR on antibiotic prescribing remains to be determined; however, our experience developing this tool for a diverse group of clinics and having clinicians and clinic personnel involved throughout the development process represent a roadmap for delivering evidence-based tools through CDS at the point of care.

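### The component-use model has no institution term although the tool differs by institution; if provider mix also differs, the training and gender contrasts may absorb a usually small part of that difference

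*Protocol article*

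**What the plan says.** The Statistical analysis section of the protocol article sets out two models. Both are three-level logistic regressions with random effects for practice and for provider within practice.

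- For the primary and other clinical outcomes: "A fixed effect will be included for intervention and for randomization strata". Institution enters through the strata, because "Stratification was by institution and by the number of patient visits to the clinic in the previous year" (Randomization section).
- For use of tool components by provider training and gender, the listed terms are a "random effect for practice and for provider within practice with fixed effects for provider training and gender". Neither institution nor strata is named.

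Other sections say that the tool was not the same at the two institutions. The Alerts section, after describing the standard alert used at Wisconsin, adds: "In addition to this alert, the University of Utah placed an additional tab in NoteWriter". Under Comparing workflows, the Utah documentation route is one in which the history, vital signs and, where used, the "structured physical exam then populates the iCPR tool". The Discussion states that the effort to fit clinic workflows "led to variations in the tool design and workflows between the two health systems". Table 1 gives 12 intervention clinics at Wisconsin and 6 at Utah. It does not give the training or gender mix at either.

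**The concern.** The outcome of this model is use of the tool's components, and the components and the route to them differ by institution. A difference between Wisconsin and Utah in, for example, calculator completion is therefore plausible from the article's own description. If one provider type is also more common at one institution, type and institution are partly confounded, and the model has no term that separates them directly.

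The practice random effect helps, because every practice lies in one institution. But a random intercept does not confine the comparison to providers within the same clinic. It keeps some weight on contrasts between clinics, and those contain the institution difference. What passes through would appear in the training or gender coefficient and could be read as a trait of the provider when it reflects the local build of the tool.

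**Working it through.** The article gives no figure to reproduce, so the check asks how much of an institution difference would reach the training contrast when training has no true effect.

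**Inputs from the article**
- Intervention clinics: 12 Wisconsin, 6 Utah (Table 1).
- Providers per clinic, over all clinics: 268/22 = 12.2 and 111/11 = 10.1. I use 12 and 10, giving 144 + 60 = 204 providers in 18 clinics, on average 204/18 = 11.33.
- Encounters per provider: 52,457/(268 + 111) = 138. This serves only as a rough scale.

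**Assumed, because the article does not give them**
- Share of one provider type, Wisconsin/Utah: 30/30, 30/40, 20/40 or 20/60%.
- Institution odds ratio for component use: 2 or 4.
- Clinic variance 0.1 to 0.3 and provider variance 0.3 to 1.0 on the log-odds scale.
- Training mix even across an institution's clinics, or concentrated in some of them.

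**Formula (approximate, logit scale, mix even across clinics).** Let d be the institution log odds ratio. A random-intercept fit gives between-clinic contrasts the relative weight

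λ = v / (v + m·s²),

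where v is the variance of a provider's observed logit, m the mean number of providers per clinic, and s² the clinic variance, enlarged by the unmodelled institution difference. The share of d that passes into the training contrast is

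λ·C / (W + λ·B),

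where W and B are the within-clinic and between-clinic sums of squares of the training indicator, and C is its cross-product with institution.

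**One case by hand:** mix 20/40, institution OR 2 (d = 0.693), clinic variance 0.1, provider variance 1.0.
- v = 1.0 + 1/(138 × 0.25) = 1.029, taking a use rate near one half; this addition is small in any case.
- s² = 0.1 + 0.693² × (12/18) × (6/18) = 0.1 + 0.107 = 0.207.
- λ = 1.029/(1.029 + 11.33 × 0.207) = 0.305.
- W = 144 × 0.2 × 0.8 + 60 × 0.4 × 0.6 = 37.44.
- C = (144 × 60/204) × 0.2 = 8.47, and B = (144 × 60/204) × 0.2² = 1.69.
- Share = 0.305 × 8.47/(37.44 + 0.305 × 1.69) = 6.8%. Spurious OR = exp(0.068 × 0.693) = 1.05.
- Without the practice random effect λ = 1, and the share is 8.47/(37.44 + 1.69) = 21.6%.

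Generalised least squares with individual providers allocated to the type gives 7.7% and OR 1.055 for this case. It is a little above the hand result because chance unevenness moves some of the training variation from within clinics to between them.

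**All settings, by generalised least squares**

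| Mix, Wisconsin/Utah | Share of institution difference passed on | Spurious OR | Share without practice effect |
|---|---|---|---|
| 30/30% | about 0 | about 1.00 | about 0 |
| 30/40% | 0.4–5% | 1.00–1.05 | about 10% |
| 20/40% | 1–13% | 1.01–1.11 | about 22% |
| 20/60% | 2–25% | 1.03–1.24 | about 39% |

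The upper ends need a small clinic variance relative to the provider variance, and provider types concentrated in certain clinics. The odds ratios fall below 1 if the provider type is commoner where use is lower.

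**Second method.** A simulation fitted random-intercept models to provider-level logits, with 400 replicates per scenario, clinic SD 0.5, provider SD 1.0 to 1.5 and an institution difference of 1 to 2 log-odds (OR about 2.7 to 7.4). At a 15/35% mix the spurious OR is about 1.05 to 1.09. At 10/50% it is about 1.11 to 1.27, with a false-positive rate of 8 to 17%.

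**With an institution term.** The bias is 0.000 in every least-squares setting and at most 0.04 log-odds in the simulation, where the false-positive rate is 4 to 7%. The standard error changes by under 5% in the simulation and by about 6% at most in a least-squares check.

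**The case against.** Four arguments stand against the point.

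1. *The bias is conditional and mostly handled.* It needs a provider mix that differs by institution, which no part of the article shows. The practice random effect, in the same sentence of the plan, already removes most of what would leak. At the 15/35% mix the simulated bias of 0.05 to 0.09 log-odds is well below the standard error of 0.19 to 0.29. The larger figures combine several unfavourable assumptions. All of this stands, and it limits the size of the point.

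2. *The two models need not match.* A reader might infer that the component-use model contradicts the clinical-outcome model by dropping its terms. The article does not support that. Strata belong in the clinical-outcome model because clinics were randomized within them, whereas comparing provider types is not a randomized comparison. Nor does the clinical-outcome model hold a separate institution term. The reason to add one here is that the tool differs by institution.

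3. *An extra covariate could be left to the statistical analysis plan.* That plan might well add it. But the article writes this model out with its fixed effects, so the point concerns a specification that is stated, not one that is missing.

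4. *Institution differences are seen elsewhere.* The evaluation framework plans to report utilization by clinic and institution, and there is a subgroup analysis by institution. These would show an institution difference beside the provider comparison. They do not adjust the training and gender contrasts.

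The calculations have limits too. Both use approximations on the logit scale, not the planned three-level logistic fit, and neither ran a separate gender scenario; gender follows by the same argument only if its mix differs by institution.

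**Conclusion.** The point holds as a conditional one. As written, the component-use model lets a usually small part of any institution difference in uptake pass into the training and gender contrasts, provided the mix of providers differs by institution. With no true effect, the spurious odds ratio is 1.00 at equal mix, about 1.01 to 1.11 at moderate imbalance, and up to about 1.2 to 1.3 only when an extreme imbalance is assumed together with other unfavourable values. The mixes, variances and institution effects are all assumptions.

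A reader might go further and conclude that the provider contrasts are biased. The article does not support this, since it gives no provider mix by institution. The concern is confined to a process outcome and leaves the primary outcome and the safety measures alone. It is an optional improvement.

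**What to change.** Add institution as a fixed effect to the component-use model, so that provider training and gender are compared within institution. The full randomization strata are not needed for this purpose, and their effect on precision over 18 clinics was not examined. Centring the provider covariates on their clinic means would also remove the leak.

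The cost is one term, using a variable already held and already used in the randomization, and a change of a few percent in the standard error. A table of provider training and gender by institution in the intervention clinics would show readers whether the condition for bias is met.
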